## Abstract

**Background:**

Video-assisted thoracoscopic surgery (VATS) is a key treatment for many cardiothoracic issues, but intraoperative factors can lead to acute postoperative pain (APSP), impacting recovery and quality of life. While multimodal analgesic methods are used, they have notable side effects. Repetitive transcranial magnetic stimulation (rTMS) offers a non-invasive pain relief option by stimulating the primary motor cortex (M1), effective in chronic pain management. However, its role in preventing and treating APSP after VATS needs confirmation through high-quality clinical trials.

**Methods/design:**

In this single-center, prospective, double-blind, randomized controlled trial, a total of 260 patients slated for VATS will be randomly allocated in a 1:1 ratio to either an active rTMS group or a sham rTMS group. Both groups will receive a 20-min intervention at two specified time points: (1) the afternoon before the surgery while in the ward, and (2) 30 min before the surgical procedure on the day of the operation. The primary outcome measure is the incidence of moderate-to-severe pain at 24 h following surgery. Secondary outcome measures encompass pain scores at rest and during movement at specified time points (T1: 2 h, T2: 6 h, T3: 12 h, T4: 24 h, T5: 48 h, T6: 90 days postoperatively), total consumption of rescue analgesics, quantified in morphine milligram equivalents (MME) within the initial 48 h, time to first request for patient-controlled intravenous analgesia (PCIA), extubation duration, length of stay in the post-anesthesia care unit (PACU), and the Quality of Recovery-15 (QoR-15) score at 24 and 48 h postoperatively. All outcomes will be assessed utilizing validated instruments.

**Discussion:**

APSP remains a significant clinical issue, affecting patient outcomes and quality of life. rTMS, a promising non-invasive technique, has shown potential in treating mental disorders, neurological conditions, and chronic pain. This study aims to provide strong evidence on the effectiveness of rTMS in reducing acute pain after VATS, potentially enhancing multimodal postoperative pain management strategies.

**Clinical trial registration:**

[http://www.chictr.org.cn], identifier [ChiCTR2500111517].

## Introduction

1

The extensive adoption of video-assisted thoracoscopic surgery (VATS) marks a significant advancement in the field of thoracic surgery. Compared to traditional thoracotomy, VATS offers numerous advantages, such as reduced postoperative pain, faster patient mobilization, shorter hospital stays, better preservation of lung function, and oncological outcomes comparable to those of tumor resection. These advantages collectively contribute to a substantial reduction in perioperative trauma, attributable to the minimally invasive nature of the procedure (1–3). Nonetheless, the term “minimally invasive” should not be misconstrued as synonymous with “pain-free.” A significant body of clinical evidence demonstrates that between 50% and 75% of patients undergoing VATS experience moderate to severe acute postoperative pain (APSP), with pain intensity potentially comparable to that associated with thoracotomy (4, 5). This pain arises from multiple mechanisms: direct compression and injury to the intercostal nerves by trocar ports, persistent stimulation of the parietal pleura and intercostal nerves by chest tubes, potential muscle spasms from surgical manipulation, and the unavoidable release of inflammatory mediators (6, 7). Inadequate control of this complex and intense acute pain has consequences extending far beyond subjective patient discomfort. This is a key factor leading to reduced lung capacity, diminished coughing ability, and retained secretions, which directly increases the risk of atelectasis and pneumonia (8, 9). Furthermore, pain restricts early ambulation, delays overall recovery, prolongs hospitalization, and increases healthcare costs. More profoundly, severe acute pain is a potent catalyst for central sensitization and is the strongest predictor for the development of chronic postsurgical pain, causing long-term physical and psychological distress (10). Therefore, optimizing APSP management after VATS is not only a humanitarian imperative but also crucial for improving outcomes, conserving healthcare resources, and preventing the transition to chronic pain.

Current standard practice for post-VATS analgesia involves multimodal strategies, typically combining regional anesthetic techniques such as paravertebral block or thoracic epidural analgesia with systemic analgesics including opioids, acetaminophen, and non-steroidal anti-inflammatory drugs (11–13). Although this approach has achieved some success, its limitations are increasingly apparent. Regional techniques carry risks of failure, operator dependency, limited duration of action, and potential complications like hypotension, nerve injury, and pneumothorax (14). Systemic opioids, as the cornerstone of analgesic therapy, pose significant clinical challenges due to their side effects: respiratory depression directly threatens pulmonary function in thoracic surgery patients; nausea, vomiting, intestinal obstruction, and constipation severely compromise rehabilitation quality and prolong hospital stays; long-term use carries addiction risks, thereby exacerbating global public health crises (15, 16). Clearly, relying solely on existing regimens makes perfect analgesia challenging to achieve. There is a pressing clinical need for innovative adjunctive therapies that work via different mechanisms, directly modulating central nervous system pain processing to reduce reliance on opioids.

Repetitive transcranial magnetic stimulation (rTMS), a non-invasive neuromodulation technique, generates controlled electrical currents in specific cortical regions, thereby enabling the permanent modulation of a group of neurons’ excitability (17, 18). rTMS has established therapeutic efficacy for conditions such as stroke sequelae, Alzheimer’s disease, Parkinson’s disease, and sleep disorders (19–21). In pain medicine, rTMS has been shown to target and modulate the “pain matrix,” including the primary motor cortex (M1), prefrontal cortex, anterior cingulate cortex, and thalamus (22). High-frequency (≥5 Hz) stimulation of the M1 region has been demonstrated to effectively treat chronic neuropathic pain and fibromyalgia (23). Its analgesic mechanisms are likely multi-faceted: (1) direct activation of M1-thalamic projections, modulating thalamic gating; (2) Enhancement of descending pain -suppressive pathways engaged by the gray matter surrounding the ventricles and the anterior ventral midline of the medulla; (3) facilitation of endogenous opioid system release; and (4) Induce synaptic plasticity changes (such as long-term potentiation or inhibition) to remodel abnormal pain networks (24–26). Given the established efficacy of rTMS in chronic pain, shifting its application earlier to the perioperative period to prevent or mitigate central sensitization and acute pain triggered by the potent noxious stimulus of surgery represents a potential paradigm shift and a logical scientific extension. Through pre-emptive or protective analgesia administered preoperatively or early postoperatively, rTMS might raise pain thresholds, rendering the central nervous system less responsive to noxious inputs.

Despite this strong rationale, the application of rTMS for controlling acute nociceptive pain following surgery remains a frontier area with scarce evidence. Existing research predominantly focuses on chronic pain, with high-quality studies targeting acute pain, especially after high-pain-intensity surgeries like thoracic procedures, being exceptionally rare.

On the basis of the above content, we formulate the core hypothesis of this study: A series of 10-Hz rTMS treatments administered to areas M1 during the perioperative period for VATS can safely and effectively reduce central pain sensitization, thereby significantly attenuating APSP intensity, decreasing rescue opioid consumption, and ultimately enhancing overall recovery quality.

## Methods and analysis

2

### Study design

2.1

A single-center, prospective, randomized controlled clinical trial conducted at the Affiliated Hospital of Jiaxing University. The study plans to enroll 260 patients scheduled for elective thoracoscopic surgery. This research protocol has been granted approval by the Ethics Review Committee of Jiaxing University Affiliated Hospital (Approval No. 2025-KY-630) and has been registered with the China Clinical Trial Registry (http://www.chictr.org.cn, Registration number: ChiCTR2500111517). Recruitment of participants is currently underway, strictly adhering to predetermined inclusion and exclusion criteria. All participants will sign written informed consent forms prior to enrollment. This study complies with the Standard Protocol Items: Recommendations for Interventional Trials (SPIRIT) guidelines (27). The flow of patient recruitment, intervention, and outcome measurement is summarized in Figure 1.

**FIGURE 1 F1:**
[figure not shown]
Flow diagram of the study.

### Eligibility criteria

2.2

Patients at Jiaxing University Affiliated Hospital who meet the criteria for VATS will undergo screening and evaluation by the research team based on predefined standards the day before surgery. Written informed consent will be provided prior to the baseline assessment (Supplementary Material 1).

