### Exclusion criteria

2.4

(1).Contraindications for rTMS (such as intracranial metal implants, pacemakers, personal or family history of epilepsy);(2).Long-term use of opioids, sedative medications, or a diagnosis of chronic pain syndrome;(3).Severe mental or cognitive dysfunction that prevents them from communicating or cooperating with the assessment;(4).History of drug or alcohol abuse;(5).Pre-operative pre-existing neurological deficits;(6).Pregnant or breastfeeding women;(7).Any other circumstances that the researcher considers unsuitable for participation in this study.

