
**TABLE 1 T1:** The study schedule for enrollment, treatments, outcome measurements, and data collection.

Study period									
Time point	Enrollment		Post-randomization						
	Pre-2	Pre-1	30 min before surgery	2 h after surgery (T1)	6 h after surgery (T2)	12 h after surgery (T3)	24 h after surgery (T4)	48 h after surgery (T5)	90 days after surgery (T6)
Enrollment									
Inclusion criteria	✓	–	–	–	–	–	–	–	–
Exclusion criteria	✓	–	–	–	–	–	–	–	–
Informed consent	✓	–	–	–	–	–	–	–	–
Randomization	–	✓	–	–	–	–	–	–	–
Interventions									
Active rTMS group	–	✓	✓	–	–	–	–	–	–
Sham rTMS group	–	✓	✓	–	–	–	–	–	–
Outcome measurement									
Postoperative resting pain score (NRS)	–	–	–	✓	✓	✓	✓	✓	✓
Postoperative movement pain scores (NRS)	–	–	–	✓	✓	✓	✓	✓	✓
Postoperative recovery quality index (QoR-15)	–	–	–	–	–	–	✓	✓	–
Remedial analgesic dosage (MME) in the first 48 h postoperatively	–	–	–	–	–	–	–	✓	–
Incidence of moderate to severe pain at 24 h postoperatively	–	–	–	–	–	–	✓	–	–
Adverse events	–	–	–	✓	✓	✓	✓	✓	✓

According to SPIRIT 2013 statement: defining standard protocol items for clinical trials. Pre-2, 2 days prior to the surgery; pre-1, the day before the surgery; MME, morphine mg equivalent; QoR-15, Quality of Recovery-15.

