#### Secondary outcomes

2.10.2

The postoperative period is defined as starting from the time of PACU admission.

(1).Time to first PCIA demand (from surgery end to first effective PCA button press with drug delivery).(2).Resting pain scores (NRS) at 2 h (T1), 6 h (T2), 12 h (T3), 24 h (T4), 48 h (T5), and 90 days (T6) postoperatively. Resting pain is assessed while the patient is lying quietly.(3).Movement pain scores (NRS) at T1–T6 postoperatively. Movement pain is assessed during turning or coughing.(4).PACU length of stay (hours from PACU admission to discharge).(5).Area under the curve (AUC) for resting pain scores from T1 to T5 (0–48 h), calculated using the trapezoidal rule, to quantify total pain burden.(6).AUC for movement pain scores from T1 to T5 (0–48 h), calculated using the trapezoidal rule.(7).Quality of Recovery assessed by QoR-15 score at 24 h (T4) and 48 h (T5) postoperatively.(8).Extubation time (minutes from cessation of all maintenance anesthetics to safe removal of the endotracheal tube). The decision to extubate, made by a blinded anesthesiologist, will be based on standard clinical criteria.(9).Record the dosage of rescue analgesics administered within 48 h postoperatively, expressed in milligram equivalents of oral morphine (MME). Rescue analgesia is administered according to the protocol if the patient’s resting pain numerical rating scale (NRS) score is ≥4 within 48 h postoperatively. For standardized comparison, all opioid medications are converted to milligram equivalents of oral morphine based on the American Academy of Pain Medicine guidelines (36).

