### Data collection and management

2.12

Data will be recorded in Case Report Forms (CRFs) and include preoperative details like demographics, pulmonary function (FEV1/FVC), surgical type (segmentectomy, lobectomy, wedge resection, other), surgery duration, and intubation type (double-lumen tube or bronchial blocker). Postoperative data will include pulmonary function, NRS scores, QoR-15, delirium, incidence of postoperative nausea and vomiting, and gastrointestinal recovery. Data were collected and managed using REDCap, a secure electronic data capture system compliant with ICH-GCP and applicable regulatory requirements. CRFs were designed according to the study protocol and CDASH standards. Real-time data validation, including range checks and logical consistency, was programmed into the system. Discrepancies and queries were resolved by investigators through the EDC platform, with all modifications tracked by an audit trail. External laboratory data were imported electronically to reduce manual entry errors. Following completion of data collection, the database underwent a final review, was locked, and then exported for statistical analysis.

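### No resting NRS, movement NRS or QoR-15 is scheduled before the first rTMS session, so the NRS and QoR-15 outcomes have no baseline covariate and 90-day pain has no reference value

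*Protocol article*

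**What the plan says.** All references are to the protocol article.

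- **Section 2.2 (Eligibility criteria)** places consent ahead of a baseline assessment: "Written informed consent will be provided prior to the baseline assessment". What is assessed is not described there or anywhere else in the text shown.
- **Table 1 (study schedule)** has three preoperative columns (Pre-2, Pre-1, 30 min before surgery). The rows "Postoperative resting pain score (NRS"), "Postoperative movement pain scores (NRS") and "Postoperative recovery quality index (QoR-15") carry a dash in all three. The NRS rows are ticked at T1 to T6, and the QoR-15 row at T4 and T5.
- **Section 2.10.2 (Secondary outcomes)** agrees. NRS at rest and on movement is taken at T1 to T6, and the recovery item reads "Quality of Recovery assessed by QoR-15 score at 24 h (T4) and 48 h (T5) postoperatively".
- **Section 2.12 (Data collection and management)** says the CRFs "include preoperative details like demographics, pulmonary function (FEV1/FVC), surgical type" and other surgical details. The pain and recovery scores appear in the next sentence: "Postoperative data will include pulmonary function, NRS scores, QoR-15, delirium".
- **Section 2.4 (Exclusion criteria)** has one pain-related item: "Long-term use of opioids, sedative medications, or a diagnosis of chronic pain syndrome". No limit is set on current pain.
- **Section 2.14 (Statistical analysis)** foresees linear or logistic regression but names no baseline pain or QoR-15 covariate.

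**The concern.** Pain and QoR-15 are patient-reported and differ between patients before any operation. A patient's own preoperative score is usually the covariate most closely related to the later score. Without it, three things are lost:

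1. **Precision** for the continuous NRS and QoR-15 outcomes, because between-patient variation that a baseline would explain stays in the residual.
2. **A check on chance imbalance** between arms in preoperative pain or recovery status.
3. **Interpretation of T6.** The Introduction and Discussion make the passage from acute to chronic pain part of the rationale. A 90-day NRS with no preoperative score cannot show whether the pain is new. Section 2.4 removes diagnosed chronic pain syndromes but not undiagnosed or recent pain.

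Section 2.1 says recruitment is under way. Once the first session has been given, a pre-stimulation score cannot be recovered for that patient.

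**Working it through.** **Step 1. Is any preoperative score scheduled?**

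| Place | Resting NRS | Movement NRS | QoR-15 | Before stimulation? |
|---|---|---|---|---|
| Table 1 | T1–T6 | T1–T6 | T4, T5 | dash in all three preoperative columns |
| Section 2.10.2 | T1–T6 | T1–T6 | T4, T5 | none stated |
| Section 2.12 | postoperative data (listed as NRS) | postoperative data (listed as NRS) | postoperative data | not in the preoperative list |
| Section 2.2 | – | – | – | baseline assessment named, content not given |

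The three places that give timing agree, and none shows a preoperative value.

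**Step 2. Does this touch the plan's own sample size?** Section 2.13 gives 70% versus 50%, α = 0.05, 80% power and 103 per group. A two-sided, continuity-corrected comparison of two proportions gives 103, so the figure reproduces. Adding baseline scores does not change it.

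**Step 3. What would the covariate be worth for the continuous outcomes?** The documents give no correlation between preoperative and postoperative scores, so r = 0.3 to 0.5 is an assumption. Under linear adjustment the residual variance is multiplied by 1 − r², and the equivalent gain in patients is 1/(1 − r²).

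| Assumed r | 1 − r² | Fall in residual variance | 1/(1 − r²) | 117 per group is worth |
|---|---|---|---|---|
| 0.3 | 1 − 0.09 = 0.91 | 9% | 1.10 | 117/0.91 ≈ 129 |
| 0.5 | 1 − 0.25 = 0.75 | 25% | 1.33 | 117/0.75 = 156 |

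Here 117 is half of 260 less the 10% dropout in section 2.13 (130 × 0.9). The gain concerns NRS scores, the pain AUCs and QoR-15. The primary outcome is binary (NRS ≥ 4, section 2.10.1), and 1 − r² does not apply to it.

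**The case against.** **The schedule is weak evidence of absence.** The Table 1 rows are labelled postoperative, so dashes before surgery follow from the labels. The table has no row for any baseline data, although section 2.12 collects some. It also omits extubation time, PACU stay and time to first PCIA demand, which section 2.10.2 lists as outcomes. The preoperative CRF list is illustrative, and Supplementary Material 1 and Figure 1 are not shown. This stands in part. The supportable statement is that no preoperative score is scheduled or stated, not that none will ever be taken. Section 2.12 still assigns both instruments to postoperative data, and a baseline score given elsewhere would have to be reconciled with Table 1.

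**There is no contradiction with section 2.2.** A baseline assessment made up of demographics and lung function fits the text. This stands: the assessment is undefined, not contradicted.

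**Validity is not threatened.** Randomisation balances preoperative status in expectation. Raw QoR-15 and raw 90-day NRS can be compared between arms, and no endpoint for the incidence of chronic postsurgical pain is defined. This stands. Covariate choice may also be left to a statistical analysis plan that is not shown, but no such plan can adjust for a value that was not collected.

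**A stronger reading is tempting.** A reader might infer that patients already at NRS ≥ 4 on entry dilute the 20-point primary contrast. The documents do not support this:

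- They give no rate of preoperative NRS ≥ 4. The 70% comes from the team's preliminary findings, and both it and the hypothesised 50% may already include such patients, in which case the contrast stays at 20 points.
- With an assumed 5% to 10% who are events whatever the treatment, applying 70% and 50% to the rest gives 0.95 × 20 = 19 to 0.90 × 20 = 18 points. Holding the control rate at 70% with a risk ratio of 50/70 in the rest gives 18.6 to 17.1 points. The answer depends on the model chosen.
- Entry with pain is possible because no pain limit is set. Recording a score excludes nobody and removes no dilution.

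**Conclusion.** The point holds as a cheap improvement, not as a defect in validity. As written, the trial has no pre-stimulation value for its NRS and QoR-15 outcomes. It gives up their most closely related covariate, cannot check chance imbalance on them, and cannot separate new from pre-existing pain at 90 days.

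The gain from adding the scores is 9% to 25% less residual variance for the continuous secondary outcomes. This rests on an assumed correlation of 0.3 to 0.5, and the correlation may differ by outcome and time point. No gain or loss is claimed for the primary outcome or for the 103 per group. The finding also rests on the text shown; a baseline score described in Supplementary Material 1 or Figure 1 would turn it into a matter of aligning those with Table 1 and section 2.12.

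**What to change.** 1. In section 2.2, state what the baseline assessment contains.
2. In Table 1 and the preoperative CRF (section 2.12), add resting NRS, movement NRS and QoR-15 at Pre-1, after consent and before randomisation and the first rTMS session. Table 1 already places randomisation and the first session on that day.
3. Prespecify the baseline value as covariate for the matching outcome: resting NRS for resting scores and their AUC, movement NRS for movement scores and their AUC, and QoR-15 for QoR-15.
4. Report 90-day NRS alongside the preoperative score.
5. Optionally, describe the primary outcome in patients with baseline NRS < 4, as a supportive analysis only.

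**Cost.** A few minutes per patient at an existing contact, plus changes to Table 1, the CRF and the analysis wording. No extra staff or invasive procedure is needed. Patients already enrolled will lack the value, so the covariate must be imputed or given a missing indicator for them. That rule should be fixed before unblinding. The gain in precision will be smaller the more patients were enrolled before the change.

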### Inclusion criteria

2.3

(1).Aged ≥ 18 years, gender not limited;(2).ASA classification I–III;(3).Proposed elective unilateral thoracoscopic surgery;(4).Voluntarily participate in this study and sign an informed consent form.

### Exclusion criteria

2.4

(1).Contraindications for rTMS (such as intracranial metal implants, pacemakers, personal or family history of epilepsy);(2).Long-term use of opioids, sedative medications, or a diagnosis of chronic pain syndrome;(3).Severe mental or cognitive dysfunction that prevents them from communicating or cooperating with the assessment;(4).History of drug or alcohol abuse;(5).Pre-operative pre-existing neurological deficits;(6).Pregnant or breastfeeding women;(7).Any other circumstances that the researcher considers unsuitable for participation in this study.

### Discontinuation criteria

2.5

(1).Intraoperative conversion to thoracotomy or extended surgical scope (e.g., pneumonectomy, pleuropneumonectomy).(2).Postoperative ICU stay exceeding 24 h, preventing effective assessment.(3).Patient or family requests withdrawal at any stage.(4).A serious adverse event occurred, leading the investigator to determine that the intervention must be terminated.

The participants have the privilege to drop out of the study at any time for any reason, and this will not affect their routine medical care. The research team will ensure appropriate care continues to be provided and will document in detail the reasons for withdrawing from the study. Additionally, the investigator may discontinue a participant’s involvement in case of severe organ dysfunction, protocol non-compliance, or occurrence of serious adverse events (SAEs).

